#### Primary outcome measure

The changes on the primary outcome measurement, the CCQ, will be analysed with the repeated measurements ANOVA technique. The dependent variable is the change in CCQ score from baseline (T1) to the end of the supervised treatment (T2). Treatment group is considered as independent variable and baseline CCQ score (T1) and centre of treatment are considered as covariates. Age, gender and severity of the disease will also be included in the model as covariates. If necessary, other covariates will be included in the model.

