### Effect evaluation

Table 2 provides an overview of the measures of the effect evaluation and the economic evaluation, and at which time point the measurements are performed.

**Table 2 T2:** Overview of measurements per time point

Measurement	T0	T1	T2	T3	T4
					

Demographic characteristics	x				

Smoking	x				

Body Mass Index	x				

Living situation	x				

Comorbidity	x				

Coping style (UCL)		x			

Medical treatment prior to admission	x				

Exacerbation severity	x				

Indication for admission	x				

Clinical COPD Questionnaire (CCQ)	x	x	x		x

EuroQol 5D (EQ-5D)		x	x		x

Satisfaction					

patient satisfaction			x		x

primary caregiver satisfaction			x		x

Caregiver Strain Index			x		x

Treatment Failures			x		

Readmissions					x

Mortality					x

Cost diary			x (IG)	x	x

Discrete Choice Experiment				x	

Lung function testing					x

6 Minute Walking Distance					x

T0 = baseline; T1 = randomisation; T2 = end of supervised treatment; T3 = follow up 1; T4 = follow up 2; IG = intervention group only

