### Data analysis

Data analysis will be performed according to the intention to treat principle. Data from patients who die, quit participation or are otherwise lost to follow up will be included in the analysis up until the point of drop out. Missing observations will be imputed or weighted appropriately.

All primary and secondary outcome measurements will be analysed using analysis of covariance. In order to control for dependency between the repeated measurements within one patient, and for the dependency between patients from the same hospital, multilevel analyses will be performed as well. We set the significance level at α = 0.05.

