### Sample Size calculation

Primary outcome is the change in the CCQ score between baseline (day 3 of admission) and the end of the supervised treatment (day 7).

Before the start of the study, a preliminary sample size calculation for an independent samples t-test was performed based on the results of a pilot study, where the average CCQ decreased from 3.8 on the day of admission to 2.6 by the end of the supervised treatment The standard deviation of that change was 1.04. With a MCID of 0.4, the required Cohen's effect size d would be 0.385 [99]. For a risk of a type-I error of 5% (α = 0.05) and a risk of a type-II error 20% (1-β = 0.80), the required sample size was 214.

However, primary outcome measure in this study is the change in the CCQ score from the third day of admission and the end of the supervised treatment (day 7), which is likely to have a stronger correlation with the baseline score. Therefore, a new sample size calculation for ANCOVA was performed after 85 patients had been treated, without breaking the randomisation code. Taking into account the correlation between the baseline score and the change (r = 0.288), as well as the standard deviations measured in the trial (0.988 for the intervention group and 0.922 for the control group), the required effect size f is 0.22 and the sample size is 165.

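### The day-1 (T0) CCQ is not named as a covariate in the primary model; prespecifying it beside the T1 score would probably add a little precision for one degree of freedom

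*Protocol article*

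**What the plan says.** The Primary outcome measure part of Data analysis takes the CCQ change from T1 (day 3, randomisation) to T2 (day 7) as dependent variable. Its covariates: "Treatment group is considered as independent variable and baseline CCQ score (T1) and centre of treatment are considered as covariates". Age, gender and disease severity follow. A closing sentence lets in further covariates if necessary, without naming any or giving a rule.

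In Table 2 (Effect evaluation) the row "Clinical COPD Questionnaire (CCQ" is marked at T0, T1, T2 and T4. Data collection puts T0 on the first day of admission and T1 on the third. The treatment section gives all patients usual care for the first three days, so both scores precede any difference between the arms. Under Setting and recruitment, early data are destroyed only if consent is not given by day 3, and consent is required before randomisation. T0 data are therefore kept for every randomised patient.

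The Sample Size calculation credits the T1 score only: "Taking into account the correlation between the baseline score and the change (r = 0.288".

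**The concern.** Two pre-randomisation scores exist on the instrument that measures the endpoint, and the primary model names one. A single score with 24-hour recall is a noisy measure of a patient's level, so an earlier score may help to predict day 7 even when day 3 is known. T0 has at least as good a claim to a place in the model as age or gender, which are named.

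What is at stake is precision. The planned total fell from 214 to 165, partly through adjustment for baseline. The open clause does not secure the gain: if T0 is added under it after results are seen, the choice can look data-driven; if it is never added, whatever precision it holds is lost.

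**Working it through.** **Inputs from the Protocol article.** From Data analysis: "We set the significance level at α = 0.05" (taken as two-sided). From Sample Size calculation: "a risk of a type-II error 20% (1-β = 0.80"; target difference 0.4 ("With a MCID of 0.4, the required Cohen's effect size d would be 0.385"); pilot change from admission to end of supervised treatment ("The standard deviation of that change was 1.04"); in-trial SDs 0.988 and 0.922; r = 0.288.

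**Step 1: reproduce the plan's figures.**
- Preliminary calculation: d = 0.4/1.04 = 0.385, and a two-sample t-test with d = 0.385 gives 214 in total, matching "the required sample size was 214".
- Pooled SD of the T1-T2 change = √[(0.988² + 0.922²)/2] = 0.956.
- Residual SD given T1 = 0.956 × √(1 − 0.288²) = 0.915.
- f = 0.4/(2 × 0.915) = 0.2186, stated as 0.22.
- F test with 1 numerator df, two groups and one covariate (noncentrality f²N): N = 165 at f = 0.22, with power 80.2%. With unrounded f, N = 167, and power at 165 is 79.7%.

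The stated sample size holds with T1 alone.

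**Step 2: what adding T0 does.** Let p be the partial correlation of T0 with T2 given T1. Residual variance is multiplied by (1 − p²), f becomes 0.2186/√(1 − p²), and one more df is spent. The documents do not give p, so it needs assumptions:
- equal SDs s at T0 and T1, from 0.8 to 1.2;
- T0-T1 correlation r01 from 0.6 to 0.8;
- r negative (patients with worse scores improve more);
- the pilot SD of 1.04 applied to the T0-T2 change.

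These give:
- SD(T2)² = s² + 0.956² − 2 × 0.288 × s × 0.956
- r12 = (s² − 0.288 × s × 0.956)/(s × SD(T2))
- r02 = (s² + SD(T2)² − 1.04²)/(2 × s × SD(T2))
- p = (r02 − r01 × r12)/√[(1 − r01²)(1 − r12²)]

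Example, s = 1.0 and r01 = 0.7: SD(T2) = √(1 + 0.913 − 0.550) = 1.167; r12 = 0.725/1.167 = 0.62; r02 = (1 + 1.363 − 1.082)/2.335 = 0.55; p = 0.204, so p² = 4.2%.

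| s | r12 | r02 | p² at r01 = 0.6 | p² at r01 = 0.7 | p² at r01 = 0.8 |
|---|---|---|---|---|---|
| 0.8 | 0.50 | 0.40 | 2.0% | 0.6% | 0.0% |
| 1.0 | 0.62 | 0.55 | 7.9% | 4.2% | 1.2% |
| 1.2 | 0.71 | 0.66 | 16.8% (excluded) | 10.1% | 4.4% |

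**Step 3: plausibility bound.** The 16.8% cell needs day 1 to predict day 7 (0.66) better than day 3 (0.60). Requiring r01 ≥ r02 moves the limit at s = 1.2 to r01 = 0.657, where p² = 12.8%.

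**Step 4: power at N = 165 (unrounded f).**
- s = 0.8: 79.7% to 80.5%
- s = 1.0: 80.2% to 82.8% (81.3% at r01 = 0.7)
- s = 1.2: 81.4% to 84.8%

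At the upper limit the effective sample size is 165/(1 − 0.128) = 189, about 24 more patients. In the middle case it is 165/(1 − 0.042) = 172, about 7 more.

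**The case against.** The strongest reply is that nothing here is wrong. Adjusting for the score taken at randomisation, which is also the start of the change score, is standard ANCOVA; it is unbiased, and it agrees with the sample-size calculation. All of that stands. A reader might infer from the omission that the trial is underpowered or the primary estimate flawed, and the document supports neither.

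A reader might also infer that T0 is excluded, or that T1 is the only adjustment. Neither is so. The model already holds centre, age, gender and disease severity, and its last clause would allow T0. Multilevel analyses of the repeated measurements are planned too, without named time points, and an analysis plan that is not shown may settle the list. T0 is therefore unnamed in this document rather than ruled out. The clause still gives no rule, so it does not secure the use of T0.

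The gain is not established. No correlation involving T0 is reported. T1 lies closer in time to T2 and may carry all that T0 knows; the gain is then nil and one df is spent. The range above conditions on T1 alone, so the gain beyond the other covariates may be smaller. It also mixes a pilot SD with in-trial SDs, although the trial randomises only patients whose respiratory complaints have eased since day 1. A gain of 17% is tempting to quote, but it depends on the combination excluded in step 3. Equal correlations among all CCQ scores would give 11% to 17%, but they do not fit the SDs used here, which put r02 below r12 at every s.

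Finally, one might extend the same adjustment to month 3. The Secondary outcome measurements section defines long-term effectiveness over time points starting at day 1, so T0 is already part of that outcome and the extension does not follow.

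**Conclusion.** The point holds as an inexpensive improvement, not as a fault. A valid pre-randomisation CCQ score, scheduled and retained for every randomised patient, is not prespecified in the primary model. Under the assumptions and bound above, naming it would remove from nil to roughly 13% of residual variance and take power at 165 from just under 80% to at most about 85%. At s = 1.0 and a T0-T1 correlation of 0.7 the figures are about 4% and 81%. The low part of this range is easier to defend than the top.

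**What to change.** In the Primary outcome measure part of Data analysis, name the T0 CCQ as a fixed covariate beside the T1 CCQ, before unblinding, instead of leaving it to the open clause. State that missing T0 values are filled from pre-randomisation data only, so that no randomised patient drops out of the model for lack of a T0 score. The Table 2 footnote labels T0 as baseline while the primary model gives that label to T1; the same edit can say which is meant. Leave the month-3 outcome as it is.

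Cost: one sentence in the plan, one degree of freedom and no new data. Blinded pooled data from the 85 patients already treated at the recalculation could show the likely gain beforehand.

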#### Secondary outcomes measurements

All time-to-event outcomes (i.e. time to readmission and time to death) will be analysed using Kaplan-Meier curves and Cox Proportional Hazards regression model. Event rates (i.e. treatment failures, readmission rates and mortality rates) will be analysed using an appropriate model for count data (e.g. poisson regression or binomial regression)

Differences in outcomes defined as the mean change from baseline (e.g. long-term effectiveness, primary informal caregiver burden, patient- and primary informal caregiver satisfaction and quality of life) will be analysed using repeated measurements ANOVA.

Patient- and caregiver preference for place of treatment will be analysed using a logistic regression model.

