### Research questions

Our primary research question is: "What is the effectiveness and cost-effectiveness of an early assisted discharge intervention compared to hospital care as usual for patients hospitalised with an exacerbation of their COPD." The primary measure of effectiveness will expressed by the change in health status, measured by the change in Clinical COPD Questionnaire (CCQ) [38] scores between randomisation and day 7, while costs include COPD-related health care costs, patients' and informal caregivers' out-of-pocket costs and patients' and informal caregivers' costs of production loss.

The following secondary research questions will be addressed:

1) What is the long-term effectiveness of early assisted discharge compared to hospital care as usual?

2) What is the difference in treatment failures between the early assisted discharge scheme and usual care in hospital?

Treatment failure in the intervention group is defined as readmission before day 7 or death before day 7. In the control group treatment failure is defined as death before day 7 or clinical deterioration leading to prolongation of hospital stay after day 7.

3) What is the effect of early assisted discharge on readmission rates after discharge from hospital or the early assisted discharge scheme, in comparison with usual care in hospital?

4) What is the effect of early assisted discharge on mortality after discharge from hospital or early assisted discharge scheme, in comparison with usual care in hospital?

5) What is the effect of early assisted discharge on patients quality of life in comparison with usual care in hospital?

6) What is the effect of early assisted discharge on primary informal caregiver burden in comparison with usual care in hospital?

7) How is patient and primary informal caregiver satisfaction with the early assisted discharge scheme compared with usual care in hospital?

Additionally a discrete choice experiment (DCE) is performed in order to provide more insight in patient and primary informal caregiver preferences for different treatment characteristics.

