#### Secondary outcome measurements

Main secondary outcome measurement of the study is the cost-effectiveness. This will be discussed in the economic evaluation section. The following other secondary measurements will be performed. These correspond with the secondary research questions from the last paragraph of the introduction:

1. Long-term effectiveness, measured with the CCQ change over the time points from day 1 to the end of the follow-up period (T4).

2. Number of treatment failures.

3. Number of readmissions to hospital and time to readmission during the three months follow-up period.

4. Mortality and time to death during the three months follow-up.

5. Generic health related quality of life, measured with the EuroQol (EQ-5D) 5D [41]. The EQ-5D will also be used to calculate quality adjusted life year (QALYs), discussed in the economic evaluation section.

6. Effects on primary informal caregiver burden measured by the Caregiver Strain Index [42].

7. Patient and primary informal caregiver satisfaction with the program. We use a translated version of the satisfaction questionnaire used by Ojoo et al. [24] and extended it with additional questions.

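### Kaplan-Meier curves for time to readmission, with death handled as drop-out, slightly overstate the three-month readmission risk; cumulative incidence with death as a competing event should replace them

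*Protocol article*

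**What the plan says.** Under Secondary outcome measurements, the protocol article lists as item 3 "Number of readmissions to hospital and time to readmission during the three months follow-up period" and as item 4 "Mortality and time to death during the three months follow-up".

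Under Data analysis, Secondary outcomes measurements, one method is fixed for both: "All time-to-event outcomes (i.e. time to readmission and time to death) will be analysed using Kaplan-Meier curves and Cox Proportional Hazards regression model". The next sentence adds a second analysis: "Event rates (i.e. treatment failures, readmission rates and mortality rates) will be analysed using an appropriate model for count data", with Poisson and binomial regression as examples.

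The opening of Data analysis sets the rule for incomplete follow-up: "Data from patients who die, quit participation or are otherwise lost to follow up will be included in the analysis up until the point" of drop-out. Death therefore falls in the same class as withdrawal and loss to follow-up.

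Death and readmission are joined in one place only, under Research questions: "Treatment failure in the intervention group is defined as readmission before day 7 or death before day 7". For the control group, failure is instead death before day 7, or deterioration that prolongs the stay beyond day 7.

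**The concern.** Kaplan-Meier treats a censored patient as someone who could still have the event later, and passes that patient's share on to those who remain. This is reasonable for a patient who moves away. It is not reasonable for one who has died, because that patient can never be readmitted. Read as a risk, one minus Kaplan-Meier describes a setting in which nobody dies first. It is too high as soon as a patient dies unreadmitted and a later readmission is observed.

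Readmission is secondary research question 3 and a natural safety question when patients go home on day 4. The article's Background says that exacerbations and admissions raise both mortality and readmission risk, so death before readmission is foreseeable. At stake are the absolute readmission risk that readers take from the curve, and whether the readmission analysis on its own can reveal an arm with more deaths.

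The general statement that missing observations will be imputed or weighted does not settle this. Readmission after death is not a missing value.

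**Working it through.** **Inputs.** The article gives no readmission rate, death rate, event count or power for time to readmission, so there is no stated figure to reproduce on this point. All rates below are assumptions. The revised total of 165 patients (Sample Size calculation) is used only for scale in step 4.

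**Step 1. Excess for a given real readmission proportion.** Let R be the proportion really readmitted by three months and D the proportion who die first without readmission. With constant cause-specific hazards:

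- total hazard = −ln(1 − R − D)
- readmission hazard = total hazard × R/(R + D)
- one minus Kaplan-Meier = 1 − exp(−readmission hazard)

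| R | D | Total hazard | Readmission hazard | 1 − KM | Excess (points) |
|---|---|---|---|---|---|
| 30% | 2% | 0.386 | 0.362 | 30.3% | 0.3 |
| 30% | 5% | 0.431 | 0.369 | 30.9% | 0.9 |
| 30% | 10% | 0.511 | 0.383 | 31.8% | 1.8 |
| 40% | 10% | 0.693 | 0.555 | 42.6% | 2.6 |

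**Step 2. The same relation from the other side.** Now fix what the Kaplan-Meier curve shows, K, and let M be the three-month death probability that would apply if readmission did not intervene. With a = −ln(1 − K) and b = −ln(1 − M):

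- cumulative incidence of readmission = a/(a + b) × [1 − exp(−(a + b))]
- readmission or death = 1 − (1 − K)(1 − M)

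At K = 30%, the cumulative incidence is 29.7%, 29.3%, 28.6%, 27.8% and 27.1% for M = 2%, 5%, 10%, 15% and 20%. Over K from 20% to 40% and M from 2% to 20%, the curve is too high by 0.2 to 3.8 percentage points, or about 1% to 11% in relative terms.

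**Step 3. Two arms with the same readmission hazard but different mortality.** Take K = 30% in both arms, so a = 0.357.

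| | M = 5% (b = 0.051) | M = 15% (b = 0.163) |
|---|---|---|
| 1 − KM, readmission | 30.0% | 30.0% |
| Cumulative incidence, readmission | 29.3% | 27.8% |
| Readmission or death | 33.5% | 40.5% |

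The Kaplan-Meier curves coincide although one arm has three times the death probability. Cumulative incidence of readmission alone makes the arm with more deaths look better by 1.5 points. Only the combined outcome shows it as worse, by 40.5 − 33.5 = 7 points.

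**Step 4. Scale.** With 165/2 = 82.5 patients per arm and 30% readmitted, the standard error of a difference in proportions is √(2 × 0.30 × 0.70/82.5) = 7.1 points, so a 95% interval is about ±14 points. If 30% are really readmitted in both arms but 2% die first in one and 10% in the other, the curves differ by 31.8 − 30.3 = 1.5 points, about one fifth of that standard error.

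**The case against.** The strongest reply has four parts.

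- **Deaths are examined elsewhere.** Mortality is research question 4. It is a listed outcome with its own time-to-event and event-rate analyses, and death before day 7 is a treatment failure in both arms. This stands. A reader might infer that an arm with more deaths would go unnoticed, but the article does not support that. The blind spot is confined to the readmission curve. What remains is that no outcome joins the two events beyond day 7, and the one that does so before day 7 has different components in the two arms.
- **The real proportion can come from the rate models.** Binomial regression on the proportion readmitted, with few other losses, would give what cumulative incidence shows at month 3. This stands in part. The article leaves the choice between Poisson and binomial open, and that analysis does not correct the curve.
- **The Cox model is sound.** This stands. With death censored it estimates a cause-specific hazard among patients still alive and at risk, and deaths do not mechanically lower it. A reader might infer that the Cox comparison is invalid, or that the 1.5-point gap in step 4 is pure artefact. Neither follows. The two readmission hazards there are 0.362 and 0.383, a ratio of about 1.06, so survivors in the second arm really are readmitted somewhat faster. The gap misleads only when read as a difference in risk.
- **Censoring at death is inferred, and a condensed article may leave such detail to a fuller document.** The article indeed never says that death is censored for readmission. But it does name the estimator for this outcome, and it does class death with drop-out. Applied as written, those two statements give censoring at death.

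**Conclusion.** The point holds and is minor. As written, the plan censors deaths in the readmission curve, so one minus Kaplan-Meier overstates the three-month readmission risk. The direction does not depend on the assumed rates, but the size does. Under constant hazards and 30% really readmitted, the excess is about 0.3, 0.9 or 1.8 points with 2%, 5% or 10% dying first. In the wider range tried it reaches 3.8 points, at 20% mortality. In a trial of this size that is small against sampling error, and it is unlikely to change a conclusion by itself.

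The readmission curve also cannot show excess deaths. That limits this one analysis and does not mean the trial ignores mortality. Kaplan-Meier is appropriate for time to death, and the Cox hazard ratio for readmission is valid if labelled for what it is. The primary CCQ comparison and the sample size are untouched.

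**What to change.** Under Data analysis, Secondary outcomes measurements, treat the two outcomes separately:

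- **Time to readmission:** replace the Kaplan-Meier curve with the cumulative incidence function (Aalen-Johansen), with death as a competing event. Show the cumulative incidence of death beside it, since step 3 shows that the readmission curve alone can flatter the arm with more deaths.
- **Cox model for readmission:** keep it, and report the result as a cause-specific hazard ratio.
- **Companion analysis:** add time to readmission or death over three months, defined identically in both arms.
- **Time to death:** keep Kaplan-Meier and Cox as planned.

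Under Data analysis, state that for readmission death is a competing event and not drop-out.

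The cost is a change of wording and one extra analysis. Readmissions and mortality are already collected (Table 2), so no new data are needed. The reported readmission risk will read slightly lower.
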